### Safety outcome

Subjects will be fully informed about the foreseeable risks and discomforts associated with participation in this study. The consent forms describe these risks and discomforts clearly. Patients must know that they have the option to withdraw from the study at any time. Withdrawal from this study can be done without consequence. The investigators may also choose to terminate a participant from this study, if they suffer a severe adverse event, do not follow study requirements, or feel that continued participation would put the person at a greater risk than indicated. Headaches, itching, and paresthesia are generally very mild with tDCS and are limited to the actual treatment duration. Since skin nerves habituate to the electrical stimulation rather quickly, most subjects are not aware of the stimulation after about the first 1 min. This is what allows sham stimulation to be effectively masked. More persistent headache can be treated with acetaminophen or ibuprofen. The range of stimulation intensities for human studies of tDCS is usually 1–2 mA as we do in our study. Skin redness is common with tDCS studies because the electrical stimulation increases local blood flow under the electrodes. This redness should dissipate within 30 min or less. There should be no evidence of redness or skin breakdown before the tDCS application.

### Sample size estimation

Based on a recent study in the field using single-session bilateral tDCS over the DLPFC compared to sham tDCS [31], we estimated an effect size of 0.55. To demonstrate the intervention effect in the primary outcome, 64 participants (32 per tDCS group) need to be included in the analysis with a two-group *t*-test with a 0.05 two-sided significance level and a power of 80%. Sample size estimation was conducted using PASS software [47].

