## Methods/design

### Design and setting

This study is conducted according to a double-blind randomized sham-controlled design, and it is a single-center superiority trial, which was conducted at the National Brain Mapping Lab, Tehran, Iran. The study is currently recruiting and 64 subjects with obesity or overweighed between the age of 18 and 61 years are to be randomly divided into two parallel arms which deliver active or sham DLPFC tDCS. A single-session bilateral tDCS over the DLPFC is applied in half of the subjects while the other half receives sham stimulation.

The course of the trial is visualized in Fig. 1.

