### Participants

We plan to enroll 64 subjects from specialized nutrition clinics by flyer advertising. We also made a video to get people more familiar with our project. Participants must follow all of the inclusion criteria below:
Age ≥ 18 and < 61 years oldRight-handednessPersian speakingBMI: 25–35 kg/m^2^Frequent food cravings (≥ 3 per day during last month, as assessed by self-report questionnaire)Being responsive in food cue-reactivity screening at baseline (defined as mean craving scores (> 70) in food-related images on the Visual Analog Scale (0–100))

The participant with any of the following criteria will be excluded from the study:
Unwillingness or inability to complete any of the major aspects of the study protocol including food cue rating or behavioral assessmentsComorbid psychiatric disorders (i.e., depressive, bipolar, or psychotic disorders), which are evaluated by a mental health specialistActive suicidal ideation with intent or plan as determined by self-report or assessment by a mental health specialist during the initial screening or any other phase of the studyUnstable medical disorder reported in subject’s medical history or by a clinician assessmentNon-correctable vision or hearing problemsPersonal or family history of seizuresHistory of strokeAny other condition the research team feel would put the subject at risk for entering the studyContraindication to tDCS (pacemaker, a metal embedded in the scalp or brain, skin lesions at the site of stimulation, and history of head injury or neurosurgery) and MRI (claustrophobia, metallic implants, ferromagnetic metals in the scalp or brain, and pregnant women)

Concomitant care and interventions prohibited during the trial will be the recent use of diabetes medication or insulin injection or a medical indication for use during the study period, the use of medications that can affect appetite or weight (e.g., orlistat, sibutramine, topiramate, bupropion), and participation in weight loss program or non-invasive brain stimulation therapy during the study.

If all eligibility criteria are reached and participants provide written informed consent for study participation, they will be included in the study sample. Eligibility will be determined by the trained study staff during screening and baseline assessments.

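### With 32 per arm and an effect size of 0.55, the planned t-test has about 58% power, not the stated 80%

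*Protocol article*

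**What the plan says.** The calculation is in the protocol article, section Sample size estimation. Citing an earlier single-session study of bilateral tDCS against sham, the authors write "we estimated an effect size of 0.55". The test is a two-group t-test at a "0.05 two-sided significance level" with 80% power, and the result is that "64 participants (32 per tDCS group) need to be included in the analysis".

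Other sections bear on the same figures:

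- **Design and setting** confirms two parallel arms of equal size: "A single-session bilateral tDCS over the DLPFC is applied in half of the subjects while the other half receives sham stimulation".
- **Participants** sets enrolment at the same number that must be analysed: "We plan to enroll 64 subjects from specialized nutrition clinics".
- **Plans to promote participant retention** says that the data of anyone who withdraws are removed. **Blinding and randomization** keeps unblinded participants out of the analysis.
- **Statistical methods** plans no adjusted analyses. It expects very little missing data and provides multiple imputation above 5% missing.

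The article states no pre-post correlation, variance reduction or dropout allowance.

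**The concern.** The article prints a complete power calculation: effect size, test, level, sidedness, power and number per arm. It can be checked without the full protocol or an SAP, and 32 per arm looks too few for a medium effect of 0.55 in a parallel-group comparison.

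This calculation is the only justification given for the size of a superiority trial. If the true power is well below 80%, the trial is more likely than stated to miss the effect it was designed to find. A non-significant result would then carry less weight against tDCS than a reader relying on the published 80% would give it.

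**Working it through.** **Inputs, all from Sample size estimation unless noted**

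- Effect size 0.55, read as a standardised mean difference d. The section does not name the metric, so this is an assumption.
- Two-group t-test, two-sided α = 0.05.
- n = 32 per arm, 1:1 (allocation also in Design and setting).
- Stated power 80%.

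**Attempt to reproduce the stated power**

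For a two-sample t-test with n per arm, the noncentrality parameter is λ = d·√(n/2) on 2n − 2 degrees of freedom.

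- λ = 0.55 × √(32/2) = 0.55 × 4 = 2.20
- Degrees of freedom = 62; two-sided critical value 1.999
- Power from the noncentral t distribution = **0.582**

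The normal approximation is easy to check by hand: Φ(2.20 − 1.96) = Φ(0.24) = 0.595. Neither figure is near 0.80. The probability of missing the planned effect is 1 − 0.582 = 0.418, about double the stated 0.20.

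Rounding of the effect size does not explain the gap: d = 0.545 gives 57.4% and d = 0.555 gives 58.9%.

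**Number needed for 80% power at 0.55**

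- Normal approximation: n = 2(1.960 + 0.842)²/0.55² ≈ 51.9, so 52 per arm.
- Noncentral t: 52.9, so **53 per arm, 106 in total**, before any allowance for loss.

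**Effect detectable with 80% power at 32 per arm**

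- Noncentral t: **d = 0.711**
- 0.711/0.55 = 1.29, that is 29% larger than planned.

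**Other readings that might have produced the figure**

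| Reading | Result | Fits the text? |
|---|---|---|
| One-sided 0.05 | Power 70.2% at 32 per arm; 42 per arm for 80% | No: the text says two-sided, and 80% is not reached |
| Paired or one-sample t-test | Needs 28; power 85.4% at 32 | No: the test and the design are two-group |
| 0.55 as Cohen's f | About 28 in total | No: does not give 64 |
| 0.55 on the raw-score SD, tested as a change score, pre-post correlation r | d becomes 0.55/√(2(1 − r)). Power 58.2% at r = 0.5, 67.8% at r = 0.6, 79.8% at r = 0.7 | Only with an r of about 0.7, which is not stated |

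A paired requirement of 28, inflated for 10% loss, is 28/0.9 = 31.1, so 32. That may be where the 32 came from, but this is speculation. No 10% loss is stated, and a paired calculation does not apply to two independent arms.

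**Effect of loss (illustration only; the documents give no loss rate)**

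- 29 analysed per arm (3/32, about 9% lost): power 53.9%
- 26 analysed per arm (6/32, about 19% lost): power 49.4%

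**The case against.** The strongest reply is that 0.55 is called only an effect size, with neither its metric nor its standard deviation named. The outcome in the Primary outcomes section is a change compared with a change. If 0.55 were scaled to the raw-score SD and repeated measurements correlated at about 0.7, a change-score t-test with 32 per arm would have 79.8% power, close to the claim. That is a possible origin, but it does not rescue the text. No correlation is given, the result depends heavily on it (58.2% at 0.5), and that outcome involves four VAS measurements rather than a simple pre-post pair. If this was the basis, the section still omits the input that yields 80%.

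A second reply concerns loss. This is a single-session trial, and very little missing data is expected, so all 64 may well be analysed. That is fair: the analysed number may be lower than 64, not must be. Imputation for missing values does not help where data are deliberately removed after withdrawal or unblinding, but the main finding does not depend on any loss.

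A third point limits the scope. The Abstract names ventral striatum response as primary, while the Primary outcomes section names VAS craving. The sample size section does not say which one 0.55 describes. The finding therefore concerns the stated effect size, whichever outcome it belongs to.

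**Conclusion.** The concern holds. On the section's own inputs, power is about 58%, some 22 percentage points below the stated 80%. The stated sample is 42 participants short of the 106 that those inputs require. No other section supplies an input that closes the gap.

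The conclusion rests on one assumption, that 0.55 is a standardised mean difference on the scale being tested. It takes all 64 participants as analysed, so it is the favourable case with respect to loss. The correction matters because the figure is the sole basis for the trial's size and for how a null result will be weighed.

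**What to change.** Rewrite the Sample size estimation paragraph, in the protocol and in any SAP that repeats it, to say:

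- 32 analysed per arm give about 58% power for a standardised difference of 0.55 with the two-group t-test at two-sided 0.05, and 80% power for a difference of about 0.71, assuming no loss.
- The metric of the effect size and the outcome to which it applies.
- A non-significant result will be interpreted from the confidence interval, by whether it excludes 0.55.

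If a pre-post correlation or another analysis lay behind the 80%, state it with its source and recompute. If the sponsor chooses a baseline-adjusted analysis to recover power, the restated figure should be based on that analysis, and Statistical methods, which plans no adjusted analyses, must be changed to match. The gain depends on a correlation the documents do not give. With 0.55 taken on the raw-score SD, replacing d by 0.55/√(1 − r²) gives power of 70.6% at an assumed r of 0.5, 77.3% at 0.6 and 85.8% at 0.7.

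The cost is one paragraph of wording and a less favourable stated power. No added enrolment or visits are needed. The Trial status section describes recruitment as ongoing and no interim analysis is planned, so on that status the correction can be made before results are known.

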### Statistical methods

Baseline participant characteristics will be presented as mean ± standard deviation for continuous variables or percentages for categorical variables. Participant demographics data will be compared between the active tDCS and sham tDCS groups, using a two-sample *t*-test (Student’s *t*-test).

To control for the tDCS intervention efficacy, a repeated-measures analysis of variance (ANOVA) will be performed on FCQ-T with time (before/after tDCS) as the within-subject factor and group (active tDCS/sham tDCS) as the between-group factor. The same strategy will be followed for behavioral and neuropsychological data.

Changes in functional neural parameters (resting-state and task-related fMRI) will be preprocessed and analyzed using the Analysis of Functional NeuroImages (AFNI) [48]. To assess brain–behavior associations, the correlations between changes in brain activity/connectivity and subjective craving will be investigated using the Pearson correlation test. As an exploratory analysis, the definition of major prognostic factors for response to active tDCS will be assessed using the exploratory regularized regression model. Assessment of the model validity will be performed using leave-one-out cross-validation within this dataset and will be validated with subsequent test datasets in the future studies. All statistical analyses will be run using the R Statistical Package [49]. There will be no interim analysis. The investigators will be empowered to stop the trial under the following circumstances:
Harm
There is a significant increased risk for serious adverse events, including severe itching and redness at the electrode site, nausea, dizziness, or drowsiness.Safety
Significant safety concerns emerge and the Research Ethics Committee of Iran University of Medical Sciences choose to pause or stop the trial.

We do not plan to conduct additional analyses, both subgroup and adjusted analyses.

We expect very low missing data in our baseline neuropsychological covariates and in the food craving measures (Table 1). Missing data will be reported in the publication. More than 5% missing data will result in multiple imputation with the generation of 40–50 imputed data sets to be analyzed separately and then aggregated into one estimate of the effect of the intervention on the primary and secondary outcomes. Missing data will be supplemented by the Multivariate Imputation by Chained Equations (MICE) method [50, 51].

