**Method:**

The NeuroStim-Obesity trial is a prospective, randomized, sham-controlled, double-blind single-session tDCS trial targeting food craving in those with obesity or overweighed. Once randomized, 64 adults with obesity or overweighed complete one session in which they receive either active or sham tDCS over the DLPFC (anode F4 and cathode F3, 2 mA intensity for 20 min). The primary outcome is change in neural response to the food cue-reactivity task in the ventral striatum after a single-session bilateral tDCS compared to sham stimulation. Secondary outcomes include changes in food craving evaluated by the Food Craving Questionnaire-State (FCQ-S). We will also explore the predictive role of brain structure and functional networks assessed by structural and functional magnetic resonance imaging (MRI) during both task performance and the resting-state that are acquired pre- and post-intervention to predict response to tDCS.

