#### Primary outcomes

The primary outcome is the changes from pre-fMRI to post-fMRI in VAS scores (for food craving) at post-tDCS compared to changes at pre-tDCS in the sham and active tDCS groups.

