#### Secondary outcomes

Change in FCQ-S scores from before tDCS to after tDCS, as measured by Food Craving Questionnaire-State [40]Change in resting-state functional connectivity between cortical and subcortical regions, as assessed by correlation between spontaneous BOLD signal fluctuations in subcortical ROIs and voxels within the prefrontal cortex and insula from before tDCS to after tDCSChange in resting-state functional connectivity under the stimulated area, as assessed by correlation between spontaneous BOLD signal fluctuations in the cortical area under the anode/cathode electrodes and whole brain from before tDCS to after tDCSChange in task-based functional activation in the prefrontal cortical areas and subcortical-limbic areas, as assessed by the BOLD signal changes with voxel-wise analysis in the regions of interests (ROIs) (prefrontal cortex, insula, thalamus, ventral striatum, and extended amygdala) from before tDCS to after tDCSChange in task-based functional connectivity between the cortical and subcortical regions, as assessed by psychophysiological interaction (PPI) between spontaneous BOLD signal fluctuations in subcortical ROIs and voxels within the prefrontal cortex and insula from before tDCS to after tDCSChange in task-based functional connectivity under the stimulated area, as assessed by psychophysiological interaction (PPI) between spontaneous BOLD signal fluctuations in the cortical area under the anode/cathode electrodes and whole brain from before tDCS to after tDCSChange in Resource Allocation Index (RAI) in rs-fMRI, as assessed by correlation among default mode network (DMN), saliency network (SN), and executive control network (ECN) in rs-fMRI from before tDCS to after tDCS [41]

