#### Pre- and post-assessments

The 0–100 continuous VAS will provide the possibility for assessing the self-reported food craving, hunger, and affective states in multiple time points before and after fMRI and tDCS (T1, T3, T5, and T7). Furthermore, FCQ-S and FCQ-T will provide the possibility for assessing the intensity of trait and state dimensions of food cravings before the first fMRI (T1: pre-tDCS) and after the second fMRI (T7: post-tDCS). Finally, participants will complete a questionnaire to assess blindness and potential adverse events of tDCS (T7).

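### The efficacy ANOVA is attached to FCQ-T, which is not a listed outcome; the primary VAS and secondary FCQ-S are covered only by a generic sentence that does not fix the VAS contrast

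*Protocol article*

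**What the plan says.** Under Statistical methods, efficacy is to be examined as follows: "a repeated-measures analysis of variance (ANOVA) will be performed on FCQ-T with time (before/after tDCS) as the within-subject factor", with arm as the between-subject factor. The next sentence adds: "The same strategy will be followed for behavioral and neuropsychological data". Neither VAS craving nor FCQ-S is named in that section.

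The outcome sections say something different. The primary is defined there as "changes from pre-fMRI to post-fMRI in VAS scores (for food craving) at post-tDCS compared to changes at pre-tDCS", for both arms. The first item under Secondary outcomes is "Change in FCQ-S scores from before tDCS to after tDCS". FCQ-T appears in neither list, and Exploratory outcomes does not name it.

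Under Pre- and post-assessments, FCQ-S and FCQ-T are both given at T1 and T7, for "assessing the intensity of trait and state dimensions of food cravings". VAS craving is recorded at T1, T3, T5 and T7. Sample size estimation ties a two-group t-test with 32 per arm to the primary outcome. The abstract states another primary: "The primary outcome is change in neural response to the food cue-reactivity task in the ventral striatum".

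**The concern.** The one measure singled out for the efficacy test is not a declared outcome, and the article itself labels it as the trait dimension of craving. The declared measures are left to a sentence about behavioral and neuropsychological data, which may or may not be meant to include self-reported craving.

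Two things are at stake. First, a result on FCQ-T, whether positive or null, would be reported as the efficacy result although no outcome list contains it. Second, the confirmatory test of the primary is not pinned down. An analyst could in good faith run the FCQ-T ANOVA, one of several VAS comparisons, or the t-test from the sample size section, and describe any of them as the planned analysis. The choice could be made after the data are seen.

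**Working it through.** The point concerns which quantity is tested, so the plan has no figure to reproduce here. The sample size section is used only for the test that it attaches to the primary.

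**1. Named measure against listed outcomes**

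| Measure | Listed as | Visits | Named in Statistical methods? |
|---|---|---|---|
| VAS craving | Primary (body) | T1, T3, T5, T7 | No |
| FCQ-S | Secondary (body and abstract) | T1, T7 | No |
| FCQ-T | Not listed | T1, T7 | Yes, for efficacy |

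**2. FCQ-S under the same strategy.** Two visits and two arms give a 2×2 design. The time-by-group interaction is the between-arm difference in T7−T1, which is the listed outcome. The method fits as it stands.

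**3. VAS under the same strategy.** The first scan lies between T1 and T3, stimulation between T3 and T5, and the second scan between T5 and T7. The primary compares the change across the second scan with the change across the first:

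(T7−T5)−(T3−T1) = T1−T3−T5+T7, so the weights on (T1, T3, T5, T7) are (+1, −1, −1, +1).

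Three natural ways to apply a two-level before/after factor to raw VAS scores, with the product of their weights and the primary's:

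- T7−T1: (−1, 0, 0, +1). Sum: −1+0+0+1 = 0.
- T5−T3: (0, −1, +1, 0). Sum: 0+1−1+0 = 0.
- Mean(T5, T7) − mean(T1, T3): proportional to (−1, −1, +1, +1). Sum: −1+1−1+1 = 0.

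All three are orthogonal to the primary contrast. They estimate a different effect, not a noisier version of the same one.

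**4. Two illustrations.** Suppose active stimulation lowers craving relative to sham by δ (assumed patterns, for illustration only).

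| Pattern | T7−T1 | T5−T3 | Mean after − mean before | Primary contrast |
|---|---|---|---|---|
| Lower by δ at T5 and T7 | −δ | −δ | −δ | −δ−(−δ) = 0 |
| Lower by δ at T7 only | −δ | 0 | −δ/2 | −δ |

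The conclusion can therefore depend on which reading is used.

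**5. When the ANOVA does match the primary.** Give each person two scores, D1 = T3−T1 before stimulation and D2 = T7−T5 after it. In a 2×2 ANOVA on D1 and D2, the time-by-group interaction is the between-arm difference in mean D2−D1, which is the primary as defined. With two levels and two arms, its F equals the square of the two-group t on D2−D1, with 64−2 = 62 degrees of freedom if all 64 are analysed. This is the type of test in the sample size section. Statistical methods does not say that the change scores are the data to be entered.

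**The case against.** The strongest reply is that little is wrong beyond a label. FCQ-S is a listed outcome collected at the same visits as FCQ-T, so a one-letter slip is plausible. The sentence extending the strategy can be read to cover FCQ-S and VAS. The Outcome measures section promises an active-versus-sham comparison for every outcome. The sample size section gives a two-group t-test for the primary, and a 2×2 ANOVA on the two change scores is the same test. Spelling out a derived score may be left to a fuller document.

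Much of this stands. A reader might infer that FCQ-T carries the only efficacy analysis, or that FCQ-S and VAS have no matching test at all. The documents do not support that: FCQ-S is fitted exactly by the extended ANOVA, and VAS has a suitable test if the change scores are used.

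A reader might also infer that the efficacy test would reject only about 5% of the time against a claimed 80% power. That does not hold either. The 80% is claimed for the primary outcome, not for FCQ-T. The 5% assumes that FCQ-T cannot move between T1 and T7, which the documents do not say. They label it a trait scale but schedule it again after stimulation.

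What does not stand is that nothing needs changing. The article does not merely leave out an analysis; it states one and attaches it to an undeclared measure. Whether this is a slip or intended, the section contradicts the outcome lists.

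**Conclusion.** The point holds in a limited form. Statistical methods names FCQ-T, which is not a listed outcome, for the efficacy ANOVA. The primary VAS outcome and FCQ-S are covered only by a generic sentence. That sentence is sufficient for FCQ-S but ambiguous for VAS, because a before/after factor on raw scores would not test (T7−T5)−(T3−T1).

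The orthogonality in the working follows from the definitions alone. The δ patterns are assumed and serve only to show that the readings can disagree. No loss of power or inflation of error can be put on this from the documents. Whether FCQ-T was written by mistake for FCQ-S cannot be settled from the text.

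It should be corrected before analysis because it concerns which test is confirmatory. The need is greater because the abstract and the body name different primary outcomes.

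**What to change.** In Statistical methods:

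- Replace FCQ-T with FCQ-S (T1, T7) in the 2×2 time-by-group ANOVA.
- State that the primary VAS comparison is a two-group t-test between arms on (T7−T5)−(T3−T1), or equivalently the time-by-group interaction on the two change scores. This agrees with the sample size section.
- Keep FCQ-T as a baseline descriptor or candidate predictor. If an efficacy analysis of FCQ-T is wanted, list it as an outcome.
- Settle which primary outcome applies, VAS craving (body) or ventral striatum response (abstract), and make both places agree. The primary test above presumes the body's definition.

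Adjusting FCQ-S at T7 for its T1 value is optional and not needed to resolve this point. If chosen, it would require amending the statement in the same section that no adjusted analyses are planned.

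The cost is protocol wording only: no new data, visits or participants. The described version reports that recruitment was still open, so the change can be dated before the data are analysed.

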To determine whether tDCS over DLPFC changes subcortical-limbic reactivity to food cues in obesityWhether tDCS could be an effective intervention for reducing food cravingTo determine how tDCS affects neural correspondence of craving using fMRITo determine the efficacy of tDCS on suppression of craving that influenced by individual baseline differencesTo explore which of (a) subjective, (b) clinical, (c) behavioral, (d) structural, or (e) neural circuits measures predict tDCS induced craving reduction in obesity

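### The brain–craving correlation is planned as a plain Pearson test with no term for arm; if the arms are pooled, part of the result reflects arm rather than an individual-level link

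*Protocol article*

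**What the plan says.** For brain–behaviour associations, Statistical methods names one technique: "the correlations between changes in brain activity/connectivity and subjective craving will be investigated using the Pearson correlation test". It does not say whether the coefficient is computed over all participants, within each arm, or with arm partialled out. The repeated-measures ANOVA in the same section does carry arm, with "group (active tDCS/sham tDCS) as the between-group factor". Later the section states: "We do not plan to conduct additional analyses, both subgroup and adjusted analyses".

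The third aim listed in the Background is to "determine how tDCS affects neural correspondence of craving using" fMRI. Sample size estimation gives the only standardised effect in the article ("we estimated an effect size of 0.55") and the numbers to be analysed ("64 participants (32 per tDCS group) need to be included in the analysis"). No effect size is given for any brain measure, and none for the correlation.

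**The concern.** The trial expects active stimulation to change the brain's response to food cues and also to reduce craving. If both happen, participants in the active arm sit apart from sham participants on both axes of the scatter plot. A correlation computed over everyone then picks up the gap between the two clouds as well as any slope inside them. It can be non-zero although, within each arm, people with a larger brain change have no larger craving change.

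Such a pooled correlation is a genuine marginal association, because arm drives both measures. The error would lie in reading it as evidence that individual neural change accompanies individual craving change. That is the reading a mechanistic trial invites, and the Discussion makes mechanism a main purpose. The distortion also runs the other way: a within-arm association of opposite sign to the arm shifts is diluted, and coupling that differs by arm averages out.

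Per-arm tests avoid the mixing, but significance in one arm and not in the other would not show that stimulation changed the relation.

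**Working it through.** **The plan's own figure.** The article gives no number for the correlation. Its one calculation, 64 participants for an effect of 0.55 at two-sided 0.05 and 80% power, does not reproduce: 2 × (1.96 + 0.84)² / 0.55² ≈ 52 per arm, about 104 in total. At 32 per arm the two-group t-test has about 58% power. That is a separate matter; only 0.55 and 32 per arm are carried forward.

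**Inputs.**
- From the article: 32 per arm, 1:1 allocation, two-sided 5%, and 0.55 as a craving effect.
- Assumed, because the article gives nothing: the arm shift on the brain measure (0 to 1.0), the within-arm correlation (0 as the null, then other values), normal errors and no missing data.

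**Correlation created by arm alone.** Take unit within-arm variance, within-arm correlation 0, and shifts d₁ (brain) and d₂ (craving). At 1:1 allocation arm adds d₁d₂/4 to the covariance and d²/4 to each variance:

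r = (d₁d₂/4) / √[(1 + d₁²/4)(1 + d₂²/4)]

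- 0.55 and 0.55: 0.0756 / 1.0756 = 0.07
- 0.55 and 0.8: 0.110 / √(1.0756 × 1.16) = 0.10
- 0.8 and 0.8: 0.16 / 1.16 = 0.14
- 1.0 and 1.0: 0.25 / 1.25 = 0.20
- 0.55 and 0: 0

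With N = 64 and 62 degrees of freedom, significance needs |r| ≥ 2.00 / √(62 + 2.00²) ≈ 0.246.

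**Rejection rates** (40,000 simulated trials per row, no within-arm association):

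| Shift on brain / craving | Pooled Pearson | Arm-adjusted partial correlation |
|---|---|---|
| 0 / 0 | 5.1% | 5.1% |
| 0.55 / 0 | 5.1% | 5.1% |
| 0.3 / 0.3 | 5.1% | 4.7% |
| 0.55 / 0.55 | 8.3% | 4.9% |
| 0.55 / 0.8 | 12.3% | 5.2% |
| 0.8 / 0.8 | 19.4% | 5.0% |
| 1.0 / 1.0 | 36.6% | 5.0% |

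Repeat runs at 0.55 on both gave between 8.3% and 8.8%. Nearly all of these rejections carry the sign implied by the arm shifts: about 8% in that direction and 0.6% in the other, against a nominal 2.5% each.

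**Masking.** With a within-arm correlation ρ and an equal shift d on both measures, the pooled value is (ρ + d²/4) / (1 + d²/4). For ρ = −0.35 and d = 0.55 this is (−0.35 + 0.0756) / 1.0756 ≈ −0.26. Simulated power falls from 81% (arm-adjusted) to 53% (pooled). With coupling of +0.5 in one arm and −0.5 in the other, the pooled r is 0 and 8% of trials reject, while a direct Fisher z comparison of the arms rejects in 99%.

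**What an arm comparison can detect.** The standard error of a Fisher z difference is √(2/29) = 0.263. For 80% power the difference must be (1.96 + 0.84) × 0.263 ≈ 0.74, for example r = 0 in one arm against about 0.63 in the other.

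**The case against.** The strongest reply is that the article never says the arms are pooled. Per-arm Pearson tests would remove the confounding, and a journal article may leave that detail to a fuller document. The sentence on subgroup and adjusted analyses concerns additional analyses, so it need not bar an arm term here. Both points stand, and the finding is therefore conditional on pooling. Yet the section names a specific test, gives it no arm term although the neighbouring ANOVA has one, and then says that no subgroup or adjusted analyses are planned. Pooling is the natural reading, and a reader cannot tell that the remedy is allowed.

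Two stronger readings are tempting, and the documents do not support either.
- A reader might infer that any arm effect turns into a false association. Both measures must shift; at 0.3 on both the inflation is negligible, and at 0.55 it is modest. Even then the marginal correlation is real; only its individual-level interpretation is at fault.
- A reader might infer that the third aim cannot be answered at all. That aim is loosely worded, and no hypothesis of a difference in coupling between arms is stated. The secondary outcomes on activation and connectivity, which Outcome measures and assessments says will be compared between arms, serve it in part. They do not relate brain change to craving, so they do not replace the association analysis.

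It is also fair to say that this correlation is not listed as a primary or secondary outcome and that no efficacy conclusion rests on it.

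**Conclusion.** The concern holds in a limited form. As written, the natural reading is a pooled Pearson correlation, and if stimulation shifts both measures that coefficient cannot separate the arm difference from an individual-level link. The size depends on an assumption the article does not supply, the arm effect on the brain measure: negligible inflation at 0.3 on both, 8–9% rejections at 0.55, about 19% at 0.8, and none if only one measure moves. These are rates per test. Masking of a real association is an equal reason to adjust. The consequence is for the mechanistic interpretation, not for the treatment comparison. The improvement is cheap and worth making.

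**What to change.** In Statistical methods, replace the Pearson sentence with an arm-adjusted analysis: regress craving change on brain change and arm, or equivalently partial arm out of the correlation, and report that estimate with its interval as the brain–behaviour result. Report the per-arm correlations descriptively, and add the arm-by-brain interaction as an exploratory look at whether coupling differs by arm. Say plainly that 32 per arm has 80% power only for large differences in coupling. Add a clause exempting this model from the statement that no adjusted analyses are planned.

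The cost is two or three sentences and one degree of freedom for arm (61 instead of 62). No extra data or participants are needed. The remaining drawback is the low power of the interaction: a non-significant result there must not be read as equal coupling in the two arms.
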